# Functional electrical stimulation-assisted cycle ergometry in the critically ill: protocol for a randomized controlled trial

**DOI:** 10.1186/s13063-019-3745-1

**Published:** 2019-12-16

**Keywords:** Early rehabilitation, Critically ill, Intensive care unit, Functional electrical stimulation-assisted cycle ergometry, Mobility, Physical therapy

## Abstract

**Background:**

Intensive care unit (ICU)-acquired weakness is the most important cause of failed functional outcome in survivors of critical care. Most damage occurs during the first week when patients are not cooperative enough with conventional rehabilitation. Functional electrical stimulation-assisted cycle ergometry (FES-CE) applied within 48 h of ICU admission may improve muscle function and long-term outcome.

**Methods:**

An assessor-blinded, pragmatic, single-centre randomized controlled trial will be performed. Adults (*n* = 150) mechanically ventilated for < 48 h from four ICUs who are estimated to need > 7 days of critical care will be randomized (1:1) to receive either standard of care or FES-CE-based intensified rehabilitation, which will continue until ICU discharge. Primary outcome: quality of life measured by 36-Item Short Form Health Survey score at 6 months. Secondary outcomes: functional performance at ICU discharge, muscle mass (vastus ultrasound, N-balance) and function (Medical Research Council score, insulin sensitivity). In a subgroup (*n* = 30) we will assess insulin sensitivity and perform skeletal muscle biopsies to look at mitochondrial function, fibre typing and regulatory protein expression.

**Trial registration:**

ClinicalTrials.gov, NCT02864745. Registered on 12 August 2016.

## Background

Functional disability, a natural consequence of weakness, is a frequent and long-lasting complication in survivors of critical illness [1–3]. Over recent decades, mortality from acute critical illness has decreased with a consequent increasing number of ICU survivors. Understanding the post-ICU morbidity experienced by these survivors has become increasingly important. The greatest burdens that survivors of critical illness face are related to neuromuscular dysfunction and neuropsychological maladjustment [4]. In particular, neuromuscular abnormalities during critical illness are common, with a median prevalence of 57% [1]. In both patients with chronic critical illness and survivors of severe critical illness, neuromuscular weakness may be substantial and persistent [5], resulting in important decrements in physical function and quality of life for years after discharge [1, 2].

In the past, routine features of general care provided in the ICU included liberal use of sedation and immobilization of the patient, which were thought to be necessary for facilitating interventions to normalize physiological function by artificial means. Over the last decade, there has been a paradigm shift away from this approach towards a more conservative treatment philosophy for patients in the ICU [4, 6, 7]. This paradigm shift is consistent with the observation that long-term physical problems in survivors of critical illness, particularly those with respiratory failure, may result from the protracted ICU stay and period of immobilization during which the patient is receiving organ support that is essential for survival [2, 4]. In line with this, a daily interruption of sedation policy has been widely adopted and proven to be beneficial [8] and early mobilization culture is spreading quickly across ICUs [9–13]. Indeed, these strategies, together with early physical therapy [9, 11, 12, 14–20], are the only safe [12, 20–22] and effective interventions in the prevention of long-term neuromuscular disability in survivors of intensive care. It should be stressed that in these studies early rehabilitation is defined as starting between days 2 and 5 of the ICU stay [9, 11, 12, 14–19] or as an activity beginning before ICU discharge [20].

*Standard “early” rehabilitation cannot be started early enough, and FES-CE may be a solution to this dilemma.* The first week in the ICU is critical as muscle mass and function is lost quickly. Immobility-associated muscle loss is evident as early as within 18–48 h of onset of acute critical illness or severe injury [23, 24] and is greatest during the first 2–3 weeks of critical illness [25, 26]. Up to 40% loss of muscle strength can occur within the first week of immobilization, with a daily rate of strength loss between 1.0 and 5.5% [27]. A 10–14% decrease in cross-sectional measurements of the rectus femoris muscle has been observed within the first week of the ICU stay [26]. Conventional rehabilitation during the first few days in the ICU is indeed limited in patients who are sedated and mechanically ventilated, and typically consists of passive limb movements, with or without the use of stretch reflex [16, 20]. Schweickert et al. [16] provided the earliest (within 48 h of intubation) and largest (26 ± 14 min a day for patients on mechanical ventilation) dose of rehabilitation and reported improvements of physical function at hospital discharge, but no measurements beyond. Active rehabilitation is delayed until the neurological condition of the patient improves enough to facilitate participation. In the sickest patients, who are at particular risk of developing ICU-acquired weakness (ICUAW), sedation and immobility may be prolonged well beyond the first week, when established damage to the muscle has already occurred.

There are several ways to deliver more effective physical exercise therapy to patients who are sedated and mechanically ventilated. For example, physical exercise can be delivered effectively and safely by passive supine cycling on a bicycle ergometer [15, 18, 28–30]. More recently, electrical neuromuscular stimulation (NMES) has been developed to mimic active exercise in patients who lack voluntary muscle activity [31–39]. During NMES, cutaneous electrodes placed over specific muscle groups electrically trigger muscle contractions. In order to achieve maximum efficacy, passive cycling and NMES can be delivered simultaneously and synchronized to produce a coordinated pattern of movements. The technique is called FES-CE (functional electrical stimulation-assisted cycle ergometry). There is a large body of experience with these methods in the rehabilitation of patients with stroke and spinal cord injuries (reviewed in [40]). The method is effective in preventing the loss of muscle mass [41] and has been shown to improve anabolic resistance and insulin sensitivity in quadriplegic patients [42, 43].

The only study of FES-CE in critical illness is the pilot trial by Parry et al. [44], where the feasibility and safety of FES-CE was demonstrated in a small cohort of critically ill patients (eight patients received the FES-CE intervention, versus eight controls). Patients in the intervention group showed significant improvements in the Physical Function in Intensive Care Test and a faster recovery of functional milestones (e.g. time to stand from lying, walking on the spot). However, the mechanism by which this occurred is unknown. There are no data on the effect of FES-CE on long-term functional outcome in ICU survivors. In healthy volunteers [45] and patients with spinal cord injury [46], unloaded FES-CE can increase whole-body oxygen consumption. It is unknown whether these effects, including improving insulin sensitivity and protein metabolism [47], can also be achieved in critically ill patients.

### Rationale

#### Mechanisms of muscle wasting and ICUAW

Pathophysiology of ICUAW is complex and multifactorial (reviewed in [4]), and there is a growing body of evidence suggesting the role of sarcopenia and metabolic derangement of skeletal muscle.

Firstly, *insulin resistance* is a well-known comorbidity in critical illness [48], contributing to and aggravating complications such as severe infections, organ dysfunction and death, and has also been implicated in the ICU-acquired weakness. Two main consequences of insulin resistance are hyperglycaemia and “anabolic resistance”. It has been observed that the provision of protein and energy to support the enhanced hypermetabolic demands of ICU patients is unable to prevent the rapid loss of muscle mass [49]. Indeed, skeletal muscle insulin resistance is the likely reason why nutritional support further exacerbates hyperglycaemia. Insulin therapy is often used in ICU patients to try and combat this, but it appears to be ineffective in ICU-acquired weakness and its safety in the ICU setting has been questioned [50]. Physical activity is an attractive alternative intervention target as it has profound effects on substrate metabolism in contracting skeletal muscle, with a single bout of muscle contraction known to increase muscle glucose uptake several fold and sensitize the muscle to insulin and the anabolic effects of amino acids for up to 24 h, including in individuals where insulin and anabolic resistance is evident [51]. It is not known whether intensified rehabilitation can improve the insulin effect on glucose uptake and whether it influences the stimulatory effect of insulin and amino acids on muscle protein synthesis.

Secondly, *mitochondrial dysfunction* in skeletal muscle may play a role in the development of ICUAW. Mitochondrial depletion and dysfunction of mitochondrial respiratory complexes I and IV has been demonstrated in acute severe sepsis in association with multiorgan failure and death [52], and early activation of mitochondrial biogenesis predicted survival [53]. Our group has recently demonstrated in two pilot studies [54, 55] that, compared to healthy controls, there is a 50% reduction of mitochondrial functional capacity in skeletal muscle in the patients with protracted critical illness and ICUAW. This is accompanied by a significant relative increase in the abundance and functional capacity of respiratory complex II, which delivers electrons to the respiratory chain from fatty acid oxidation [54]. Weber-Carstens et al. [48] demonstrated that insulin fails to activate GLUT-4 translocation to cellular membranes in patients with ICUAW, causing skeletal muscle “intracellular glucose starvation” and a failure of AMP-activated protein kinase to respond to the impairment of ATP production. Most notably, in five subjects, these abnormalities were alleviated by NMES. In light of this, the relative increase of complex II capacity observed in our pilot study may represent a functional adaptation of muscle to the increased reliance on fatty acid oxidation. It is not known whether the severity of mitochondrial functional alteration reflects the degree of insulin resistance and the severity of muscle weakness, and whether the delivery of very early FES-CE has a potential to influence these changes.

In the light of this, we hypothesize the following:
H_1_: As most of the damage to the structure and function of skeletal muscle occurs during the first week, intensified goal-directed rehabilitation, which includes FES-CE and starts within 48 h after ICU admission, improves the functional outcome of ICU survivors at 6 months when compared to the standard of care.H_2_: The intervention, as compared to standard of care, shall preserve muscle mass and improve muscle power at ICU discharge.H_3_: The intervention, as compared to standard of care, shall increase insulin-mediated whole-body oxidative glucose disposal and mitochondrial functional indices.

### Objectives

To investigate, in a pragmatic, prospective, randomized, controlled, assessor-blinded trial, the effects of very early intensive rehabilitation using a goal-directed protocol that includes FES-CE in mechanically ventilated ICU patients predicted to need a protracted ICU stayTo perform more detailed metabolic studies, including serial muscle biopsies and using euglycaemic hyperinsulinaemic clamps, in a nested subgroup. Insulin sensitivity in the whole study population will be compared by glucose control and consumption of intravenous insulin required to control blood glucose

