#### Standard care group

Both groups will receive usual best medical and nursing care in the ICU, which includes daily sedation holds when applicable and delirium 12-hourly monitoring (by CAM-ICU scale [58]) and management as usual in the routine practice. Respiratory physiotherapy will also be delivered without alterations. The routine standard care arm will undergo mobilization/rehabilitation delivered by personnel not involved in the study in a usual, routine way. Details of physiotherapy treatment will be recorded but not protocolled in the standard care arm.

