## Methods

### Enrolment and randomization

All patients admitted to participating ICUs are screened daily by research nurses and all eligible patients or their representatives are approached by investigators as soon as possible, but always within 72 h of admission. Participants for whom informed consent was obtained will be randomly assigned (1:1) to receive either standard care or the intervention using offsite independent randomization protocols (www.randomization.com) embedded in the electronic case report form. Randomization will be stratified according to the presence or absence of sepsis and the availability of a biopsy at baseline. There is no restriction (blocking) during randomization.

Both the study team and clinical personnel will be made aware of subject treatment allocation. The outcome assessor is not involved in patient care and remains blinded to treatment allocations.

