### Clinical data retrieval and handling

The ICUs are paperless and fully computerized, so vital functions and other physiological parameters are monitored and data are routinely stored in secure hospital data bases via a protected dedicated network (MetaVision; IMD Soft Inc.). This includes data about nutritional intake and urinary output. On top of this, research nurses will input data into an electronic, secure, customized online case report form database (eCRF; accessible at https://195.113.79.251:9090/apex/f?p=103:101:14992036032980). Data protection and encryption is in accordance with the EU’s General Data Protection Regulations as well as Czech data protection laws. The data will be audited by on a regular basis, but at least after each 10 patients are enrolled, by independent study monitor. After the database is locked upon study completion, patients’ data will be de-identified and available in full in a public database.

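### Differences in glucose control and intravenous insulin use are labelled insulin sensitivity, although both also depend on feeding and on dosing by staff who know the allocation

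*Protocol article*

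**What the plan says.** The Objectives section of the protocol article sets out the metabolic studies and then extends them to all patients: "Insulin sensitivity in the whole study population will be compared by glucose control and consumption of intravenous insulin required to control blood glucose". The sentence names the construct (insulin sensitivity) and the measure (glucose control and insulin consumption). It gives no unit, time window or denominator.

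Four other places bear on how that measure behaves:

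- *Mechanisms of muscle wasting and ICUAW* links glucose to feeding: "Indeed, skeletal muscle insulin resistance is the likely reason why nutritional support further exacerbates hyperglycaemia".
- *Standard care group* leaves general treatment to routine practice: "Both groups will receive usual best medical and nursing care in the ICU". The article states no common approach to glucose or insulin.
- *Enrolment and randomization* says "Both the study team and clinical personnel will be made aware of subject treatment allocation". The blinded person is someone else: "The outcome assessor is not involved in patient care and remains blinded to treatment allocations".
- *Clinical data retrieval and handling* describes the routinely stored ICU data: "This includes data about nutritional intake and urinary output".

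The standing of the comparison is not uniform. The abstract counts insulin sensitivity among the secondary outcomes, but the article's own *Secondary outcomes* list contains neither glucose nor insulin use. The direct measurement, a euglycaemic clamp after an overnight fast, is confined to a consenting subgroup, put at 30 in the abstract.

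**The concern.** Insulin given in an ICU answers three things at once: how sensitive the patient is, how much carbohydrate arrives, and what glucose level the staff accept before they change the dose. The planned comparison attributes the result to the first alone.

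Randomisation balances the need for feeding and insulin at baseline. It does not fix what is delivered afterwards, and those decisions are made by people who know the arm. Glucose and insulin dose also trade off: accepting a higher glucose lowers insulin use at unchanged sensitivity, so the two parts of the measure can move in opposite directions.

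At stake is the interpretation of the only evidence on insulin sensitivity outside the clamp subgroup. A difference in insulin use might be reported as a metabolic effect of the rehabilitation programme when it reflects feeding or dosing, or a real effect might be cancelled. The SF-36 primary outcome is not touched.

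**Working it through.** The plan gives no figure for this comparison, so there is none to reproduce. The check has two parts: what the measure can identify, and how sensitive a test of it would be to a shift unrelated to sensitivity.

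**What each measurement holds fixed**

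| | Clamp subgroup | Whole population |
|---|---|---|
| Intake | fasted overnight | whatever is delivered |
| Insulin | infused under a set procedure | titrated in usual care |
| Glucose | held at a normal level | whatever is achieved |
| Staff giving insulin or feed | not decisive, as the procedure fixes the conditions | aware of allocation |

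Both results carry the same name, but only the first isolates sensitivity. Assessor blinding does not close the gap, because the assessor takes no part in care and any bias would enter through care.

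**Illustration 1: a shift of any origin.** Inputs: 150 randomised 1:1, so n = 75 per arm if all contribute; two-sided 5% test (*Data analysis plan*); true effect on sensitivity zero; a between-arm shift of b standard deviations in insulin use caused by feeding or titration (assumed). The probability of a significant result is

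P = 1 − Φ(1.96 − b√(n/2)) + Φ(−1.96 − b√(n/2)), with √(75/2) = 6.12.

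| b (SD) | 0 | 0.1 | 0.2 | 0.3 | 0.4 | 0.5 |
|---|---|---|---|---|---|---|
| P | 5.0% | 9.4% | 23.2% | 45.1% | 68.8% | 86.5% |

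**Illustration 2: a shift from feeding.** Assume insulin use = carbohydrate intake ÷ sensitivity, with log-SD 0.4 for sensitivity and 0.2 for intake. The log-SD of insulin use is then √(0.4² + 0.2²) = 0.447. With intake 10% lower in one arm, the shift is |ln 0.90| ÷ 0.447 = 0.105 ÷ 0.447 = 0.236 SD, and 0.236 × 6.12 = 1.44, so P ≈ 1 − Φ(1.96 − 1.44) ≈ 0.30. A simulation of 4,000 trials per setting, using t-tests on the log scale, agrees:

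| Intake lower in one arm by | 0% | 5% | 10% | 15% | 20% |
|---|---|---|---|---|---|
| Insulin use significantly different | 6% | 11% | 29% | 60% | 87% |

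In the same simulations, insulin per gram of carbohydrate was significant in 4.6% to 5.6% of trials. That follows from the proportional model. It shows that the denominator deals with feeding; it says nothing about titration.

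**The opposite direction.** Under the same model, if the intervention raised sensitivity by 10% while intake in that arm was 10% higher, the ratio of insulin use would be 1.10 ÷ 1.10 = 1.00, and the real effect would not show.

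The documents give neither an SD for insulin use nor an expected feeding difference. The tables show how the test would respond, not what will happen.

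**The case against.** The strongest reply is that the comparison rests on one sentence in a condensed article. Unit, window, denominator and model are details that a full protocol or analysis plan commonly supplies. The article also never says that feeding or titration will differ between arms. The rationale treats hyperglycaemia as a consequence of insulin resistance, which gives glucose under feeding some standing as a marker. The formal metabolic hypothesis (H3) concerns insulin-mediated glucose disposal, which the clamp addresses directly, and the abstract goes on to place the insulin-sensitivity assessment in the subgroup. The whole-population comparison is thus supportive only.

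Most of this stands and limits the point. What survives is that the article does state what the measure will be taken to mean, and more detail on units would not by itself turn insulin requirement into sensitivity.

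A reader might infer more than the documents support:

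- *That insulin use is cumulative and so grows with ICU stay, or that glucose and insulin will be tested separately.* Neither is stated.
- *That feeds are paused around exercise sessions in one arm.* Nothing says so; fasting is mentioned only for the clamp, and the baseline procedures precede enteral nutrition.
- *That insulin infused during clamps distorts the comparison.* It is given in both arms of a subgroup of about 30, and the first clamp precedes randomisation.
- *That the adjustment list in the Data analysis plan wrongly omits nutrition.* That list follows the functional-independence analysis and is not tied to this comparison. Nutrition delivered and glucose achieved are post-randomisation variables, so their absence from a list of baseline covariates is not an error.

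**Conclusion.** The point holds in limited form. The stated measure can differ between arms with no difference in sensitivity, or fail to differ when there is one, because it also reflects nutrition delivered and titration by staff who know the allocation. On the assumed inputs, a 10% difference in carbohydrate intake raises the rate of significant results from about 5% to about 29%, and a 20% difference to about 87%. These figures depend on proportionality between insulin need and carbohydrate, on the assumed SDs and on all 150 patients contributing.

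It would go too far to say that the comparison will mislead, or that neither a positive nor a null result could be read at all. The randomised contrast in glucose control and insulin requirement remains interpretable as exactly that; it is the label of sensitivity that overreaches. With the primary outcome unaffected and the clamp providing a direct check, this is a worthwhile, inexpensive improvement rather than a serious defect.

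**What to change.** 1. Name the whole-population comparison glucose control and insulin requirement, and rest conclusions about insulin sensitivity on the clamp subgroup.
2. Analyse daily intravenous insulin per gram of carbohydrate delivered, using the stored nutrition data, over a fixed early ICU window (for example the first 7 days after randomisation while in the ICU). Present it together with mean glucose on the same days.
3. Report raw insulin use and carbohydrate intake by arm, so that any feeding difference is visible.
4. Use only baseline covariates, for example known diabetes. Corticosteroid exposure after randomisation should not be adjusted for, since it could itself be affected by allocation.
5. State as a limitation that insulin is titrated by staff who know the allocation. Dividing by carbohydrate does not remove that bias, and showing same-day glucose helps only in part.

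The cost is a change of wording, some data derivation, and a minimum-intake rule for days with little carbohydrate, where the ratio becomes unstable. The ratio also relies on rough proportionality between insulin need and intake. No glucose target, insulin rule or other aspect of care changes.
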